## Abstract

**Background:**

The reporting of outcomes in clinical trials of subjective tinnitus indicates that many different tinnitus-related complaints are of interest to investigators, from perceptual attributes of the sound (e.g. loudness) to psychosocial impacts (e.g. quality of life). Even when considering one type of intervention strategy for subjective tinnitus, there is no agreement about what is critically important for deciding whether a treatment is effective. The main purpose of this observational study is, therefore to, develop Core Outcome Domain Sets for the three different intervention strategies (sound, psychological, and pharmacological) for adults with chronic subjective tinnitus that should be measured and reported in every clinical trial of these interventions. Secondary objectives are to identify the strengths and limitations of our study design for recruiting and reducing attrition of participants, and to explore uptake of the core outcomes.

**Methods:**

The ‘Core Outcome Measures in Tinnitus: International Delphi’ (COMIT’ID) study will use a mixed-methods approach that incorporates input from health care users at the pre-Delphi stage, a modified three-round Delphi survey and final consensus meetings (one for each intervention). The meetings will generate recommendations by stakeholder representatives on agreed Core Outcome Domain Sets specific to each intervention. A subsequent step will establish a common cross-cutting Core Outcome Domain Set by identifying the common outcome domains included in all three intervention-specific Core Outcome Domain Sets. To address the secondary objectives, we will gather feedback from participants about their experience of taking part in the Delphi process. We aspire to conduct an observational cohort study to evaluate uptake of the core outcomes in published studies at 7 years following Core Outcome Set publication.

**Discussion:**

The COMIT’ID study aims to develop a Core Outcome Domain Set that is agreed as critically important for deciding whether a treatment for subjective tinnitus is effective. Such a recommendation would help to standardise future clinical trials worldwide and so we will determine if participation increases use of the Core Outcome Set in the long term.

**Trial registration:**

This project has been registered (November 2014) in the database of the Core Outcome Measures in Effectiveness Trials (COMET) initiative.

**Electronic supplementary material:**

The online version of this article (doi:10.1186/s13063-017-2123-0) contains supplementary material, which is available to authorized users.

## Background

Tinnitus is the sensation of noise ﻿such as ringing, buzzing or hissing sound perceived in the ears or head. Over 70 million people in Europe and more than 50 million people in the USA experience the condition. In few cases, tinnitus is objective with vascular or muscular causes. Most tinnitus cases are subjective, which means that the sounds are perceived only by the patient, has no clinically identifiable source of the sound and whose pathophysiology is not fully understood. This project is limited to subjective tinnitus, and so in the remainder of the article wherever we use the term ‘tinnitus’ we are referring to subjective tinnitus.

Tinnitus is a symptom that can be chronic and disabling for some. However, it is a complex condition that is challenging to manage because it is associated with a diverse range of patient complaints, including perceived loudness, sleep problems, difficulties in listening and concentration, effects on psychological wellbeing, daily life and on general health [1–3]. It may also have negative effects on personal quality of life, as well as a societal impact in terms of social withdrawal and impaired work performance [4, 5]. Each of these patient complaints could be defined as a domain (i.e. a distinct element) of tinnitus which could determine how to measure whether a treatment has worked. The process of measuring tinnitus is made all the more challenging since individual patients tend to report different profiles of tinnitus-related complaint domains. Moreover, because treatment options remain palliative rather than curative any judgements about therapeutic benefit typically concern a relative improvement and not simply a binary ‘yes/no’ or ‘present/absent’ decision.

At present, there is no consensus on what are the critically important domains of tinnitus that should be assessed to determine whether the responses to treatment are beneficial or not for patients. Our recent systematic review examining 228 published clinical trials for tinnitus, identified 35 primary domain outcomes and 60 secondary domains’ outcomes spanning nine broad categories (tinnitus percept, impact of tinnitus, co-occurring complaints, health-related quality of life, body structures and function, adverse events or harms, treatment satisfaction, treatment-related outcomes and ‘unclear or not specified’) [6]. Inconsistent outcome reporting can severely hinder identifying and interpreting the relative merits of the various interventions or therapeutic approaches that are currently on offer or under investigation [7, 8]. If all clinical trials for tinnitus used and reported results for the same set of agreed outcomes, they could be compared and combined. This would make it much easier to make sense of all the knowledge produced and reduce unnecessary research waste. The main goal, therefore, is to advance the standards for clinical trials of interventions for tinnitus by developing an agreed list of outcome domains that are critically important for determining whether a treatment has worked.

Our systematic review of 228 published clinical trials also identified at least eight broad classes of intervention strategies that have been assessed in clinical trials [6]. Each of these intervention strategies has a different targeted rationale, and is focussed on alleviating different outcome domains of tinnitus. For example, sound-based interventions, such as hearing aids and sound generators, intend to reduce loudness (e.g. [8]), whilst psychologically informed interventions are intended to improve mental health and wellbeing (e.g. [9]). Therefore, any agreed list of outcome domains is likely to be more appropriate for one intervention strategy than another. This review [6] supported an informed choice about what are the major intervention strategies to be considered in the present study. Intervention strategies most commonly reported from 2006 to 2015 were pharmacological (*n* = 66/228), electrophysiological (*n* = 59), sound therapy (*n* = 56) and psychological (*n* = 47). The majority of trials evaluating electrophysiology-based interventions are restricted to a small number of candidates recruited to experimental research studies, and so this intervention strategy is not part of standard clinical practice. Hence, a decision was made to focus the Delphi process on sound-, psychology-, and pharmacology-based interventions to create three intervention-specific Core Outcome Domain Sets.

It is vital that all key stakeholders are involved in the development of a Core Outcome Domain Set to ensure that it has broad relevance. Patients and members of the public with lived experience of a condition are valued stakeholders in the development of relevant Core Outcome Sets because they have first-hand experience of that condition [10]. These groups are henceforth collectively referred to as ‘health care users’. Instances have arisen in previous Core Outcome Set work where health care users have identified outcome domains as important that were previously overlooked [11] or previously thought to be of little importance [12] (see also [13]). One of the attractive features of the Delphi process to health care users is the ability to provide anonymity to all respondents which can offset the shortcoming of conventional means of pooling opinions obtained from a group interaction where there can be power differentials between different stakeholder groups [10, 14, 15]. Nevertheless, Core Outcome Set developers have somewhat limited experience in engaging with health care users in the process of creating consensus [10, 16], and previous studies have reported low rates of recruitment [17]. The design of the present Delphi process incorporates several different methods for promoting the involvement and participation of health care users with lived experience of tinnitus to address the secondary research question concerning what methods work well for recruiting and retaining health care users, and what methods do not work so well.

In summary, further research work is urgently needed to advance the standards for clinical trials of interventions for tinnitus by developing an agreed list of outcome domains, distinct elements of tinnitus, that are critically important for determining whether a treatment has worked, using a process that promotes input from health care users and professionals with experience in tinnitus. This protocol defines the COMIT’ID study which uses a Delphi process and face-to-face meetings to establish consensus on which outcome domains should be measured when assessing the effect of sound-based, psychology-based, and pharmacology-based interventions in clinical trials for tinnitus.

### Aims

The primary aims of the COMIT’ID study are to:Establish three Core Outcome Domain Sets, one for each of the main intervention strategies (sound-, psychology-, and pharmacology-based)Identify the key outcome domains that are common across all three Delphi processes. 

Two secondary aims are to:3.Identify the strengths and limitations of the study design with respect to methods for recruiting and for reducing attrition of health care users4.Investigate whether participation by professional experts in the Delphi process affects their subsequent use of the Core Outcome Domain Set, compared with those who do not participate.

## Methods

We will use the Delphi process to achieve a consensus of opinion from broadly representative and international expert stakeholder groups [15]. This is an observational study design comprising three independent Delphi processes, sponsored by the University of Nottingham and managed by the National Institute for Health Research (NIHR) Nottingham Biomedical Research Centre. A prospective study protocol was registered in the Core Outcome Measures in Effectiveness Trials (COMET) database [18]. This protocol describes version 2.0 (dated 14 March 2017), that was approved by the Proportionate Review Sub-committee of the West Midlands – Solihull Research Ethics Committee (REC reference 17/WM/0095, IRAS reference 220112) on 21 March 2017.

### Research steering group

A Research Steering Group has been appointed to oversee and manage the project. The group comprises international colleagues representing the identified intervention approaches (HFH, BM, AL), a patient and public involvement and engagement manager (AH) two health care users with lived experience of tinnitus, referred to as Public Research Partners (VC, BT), and the Study Management Team (KF, HS, DAH). The role of the Research Steering Group is to:Support the development of the study protocol, specifically commenting on the feasibility of the Delphi process, reviewing study documentation (e.g. advertisements, Information Sheets, video instructions for the survey, website content) and to participate in a pilot of round 1 of the Delphi surveyReview the list of outcome domains and associated descriptions, specifically commenting on the readability of the outcome descriptions, the appropriateness of the grouping of outcomes into categories and providing any additional outcomes that they believe should be included in the first round.

### Eligibility criteria for the Delphi panels

A range of expertise within the panel is considered to be an important quality criterion for development of a Core Outcome Domain Set [19]. We will, therefore, seek to include representatives from four key stakeholder groups that may be particularly interested in managing chronic subjective tinnitus in adults. Specific inclusion criteria have been defined for each stakeholder group:
*Health care users* must have the experience of living with tinnitus for 3 months or more and have had experience with at least one sound-, psychology-, or pharmacology-based intervention for their tinnitus, or have the intention of undergoing that treatment in the future
*Health care practitioners* must have a clinical qualification, be currently employed by a public or private institution that provides a tinnitus service to patients, have specific experience in assessing, diagnosing or managing chronic subjective tinnitus in adults who receive, or have received, a sound-, psychology-, or pharmacology-based intervention.
*Clinical researchers* must have an academic qualification, be currently employed by a research organisation, have current or ‘recent-past’ experience in clinical research with studies that focus on questions of clinical efficacy (benefit) of a sound-, psychology-, or pharmacology-based tinnitus intervention in humans (i.e. a co-author on a relevant peer-reviewed journal publication in the past 3 years)
*Commercial representatives* must be currently employed by a company that develops, manufactures or sells relevant sound-, or pharmacology-based product(s) that may be used for alleviating tinnitus. *Funders* must be currently contracted by an organisation that has funded tinnitus research projects addressing sound-, psychology-, or pharmacology-based interventions in the last 3 years

General eligibility for participation in the Delphi process includes men and women aged 18 years or older, with sufficient command of English to read, understand and independently complete the questionnaires. An online screening stage will ask all participants to self-certify that they ﻿are an ‘expert’ in at least one of the three tinnitus-intervention strategies.

All enrolled Delphi panellists will be eligible to register their interest in attending a 1-day consensus meeting. However, allocation of places will be limited to those respondents who complete all three rounds of the online survey. None of the Research Steering Group members will be allowed to vote on domains in the consensus meetings because this risks inadvertently introducing a power differential across participants, but they can enrol in the online Delphi surveys (with the exception of KF and HS who will have access to the dataset for all analyses). Each expert panellist is permitted to enrol for more than one Delphi process if they meet the eligibility criteria, but would be invited to attend only one consensus meeting.

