At this stage, two further revisions were made to the long-list, arising from both health care user-led and professional-led recommendations about semantic equivalence. The first was that the outcome domain ‘bothered’, defined as ‘being disturbed by tinnitus or finding it a nuisance’, was consolidated with ‘annoyance’. The second was that the outcome domain ‘frustration’, defined as ‘feeling unable to change or achieve something because of or in relation to tinnitus’, was felt to be already represented by ‘annoyance’ and ‘upset’ and, therefore, was consolidated with these. Additional file 1 reports the finalised set of 13 domain categories, 66 outcome domains, and short plain language descriptions. Categories and outcome domains will be presented within the Delphi surveys in alphabetical order to avoid potential weighting [26].

### Round 1

For each outcome domain, participants will be asked to think about the importance of each tinnitus outcome domain and indicate how important it is to measure when deciding if a sound-based/psychology-based/pharmacology-based tinnitus treatment is working. Participants will be asked to score each outcome domain using the GRADE scale of 1–9, where 1 represents least important and 9 represents most important [29]. Selecting response options 1–3 indicates that the domain is ‘not important’, whilst 7–9 indicates that the domain is ‘critically important’ in deciding whether a tinnitus treatment is effective. Scores 4, 5, and 6 indicate that the outcome domain is ‘important but not critical’. If a participant feels that they did not understand a particular outcome, they will be able to select ‘unable to score’. Following each outcome and at the end of the round, optional open-text boxes will enable participants to add any comments. In round 1, participants will be able to propose additional outcome domains. These additional outcome domains will be reviewed and coded by two Study Management Team members, with appropriate plain-language concept definitions, to ensure that they represent new items for inclusion in rounds 2 and 3. Where uncertainty exists the Research Steering Group will be consulted, and all new outcome domain terms, concept definitions and category labels will be reviewed.

### Rounds 2 and 3

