### Consensus criteria

Consensus recommendations for each intervention category will be guided by the respective round-3 results. We will include domains for which 70% or more of the participants in each stakeholder groups score 7–9, and fewer than 15% score 1–3 [30]. We will exclude domains for which 70% or more of the participants in each stakeholder groups score 1–3, and fewer than 15% score 7–9 [30]. These decisions will be taken without further discussion because time at the consensus meeting will be limited. At the consensus meeting, the moderated discussion, voting and decisions will be guided as follows:For outcomes recommended to be included based on the round-3 analysis (70% scored 7–9), domains will be included if at least 70% of participants vote ‘In’For outcomes where at least 50% of more than one stakeholder group scored 7–9 on the round-3 analysis, domains will be included if at least 70% of participants vote ‘In’For outcomes where less than 50% of the participants in all stakeholder groups or at least 50% of only one stakeholder group scored 7–9 on the round-3 analysis, domains will be included only if at least 70% of participants vote ‘In’

If consensus is not reached after two rounds of voting, a ‘majority rules’ approach will be applied.

In the very final step, the Study Management Team will seek to establish a common cross-cutting Core Outcome Domain Set by identifying those outcome domains that were voted for inclusion in all three intervention-specific Core Outcome Domain Sets.

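### Up to seven Steering Group members may score in the online rounds; their scores should be flagged, the round-3 rule run with and without them, and they should leave the uptake comparison's participant group

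*Protocol article*

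**What the plan says.** Eligibility criteria for the Delphi panels sets the bar: "None of the Research Steering Group members will be allowed to vote on domains in the consensus meetings". The only reason offered is the possible effect on the discussion, "because this risks inadvertently introducing a power differential across participants". Online scoring is treated differently: members may not vote in the room, "but they can enrol in the online Delphi surveys". Two Study Management Team members are excepted, as people "who will have access to the dataset for all analyses". The same section adds: "Each expert panellist is permitted to enrol for more than one Delphi process if they meet the eligibility criteria".

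The group's role is described in three places. Research steering group has it review the domain list, including "providing any additional outcomes that they believe should be included in the first round", and pilot round 1. The pre-Delphi section says that it informed the reduction of the 124-domain list, with the two Public Research Partners in the lead. Round 1 says of panellists' proposals: "Where uncertainty exists the Research Steering Group will be consulted, and all new outcome domain terms, concept definitions and category labels will be reviewed".

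Consensus criteria includes a domain if, in each stakeholder group, at least 70% score 7–9 in round 3 and fewer than 15% score 1–3. Of the include and exclude decisions it says: "These decisions will be taken without further discussion because time at the consensus meeting will be limited". The list that follows nevertheless puts round-3 inclusions to a meeting vote, with 70% voting In required.

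**The concern.** Steering Group members are not ordinary panellists. They helped to decide which domains are rated, and they may advise on which new ones are added. Once enrolled, their scores count in the round-3 rule and in the feedback shown to other panellists before rounds 2 and 3. Anonymous scoring deals with the power differential. It does not deal with developers' ratings counting towards the result of their own study.

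Two results are exposed. One is the round-3 status of domains near the threshold, where a stakeholder group is small. The other is the planned comparison of uptake between clinical researchers who did and did not take part: developers who enrolled would sit in the participating group, and they are the people most likely to use their own set.

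**Working it through.** **Who may score.** Research steering group lists three colleagues representing the intervention approaches, one patient and public involvement manager, two Public Research Partners and three Study Management Team members: 3 + 1 + 2 + 3 = 9. Two are excepted, so 9 − 2 = 7 may enrol, each subject to a stakeholder definition. How many will enrol, and where, is not stated.

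**Group sizes (Panel size and justification).** Sound: 60+20+20+20 = 120 to 90+30+30+30 = 180. Psychology: 40+20+20 = 80 to 60+30+30 = 120. Pharmacology: 30+10+10+10 = 60 to 60+20+20+20 = 120. The totals are 260 and 420, as stated. Groups of 10–20 occur only among pharmacology professionals. Other professional groups are 20–30 and user groups 30–90. These are enrolment targets; the rule uses round-3 respondents, so attrition would make the groups smaller.

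**Weight of one score, 100/n.** 10 points at n = 10, 5 at n = 20, 3.3 at n = 30 and 1.1 at n = 90.

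**The 70% condition.** The smallest passing count is r = 0.7n rounded up: 7 of 10, 14 of 20. Without a member, 6/9 = 66.7% and 13/19 = 68.4% both fail. One member scoring 7–9 makes them 7/10 and 14/20, both exactly 70%, which pass.

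**The 15% condition, read within each group.** Two scores of 1–3 give 2/10 = 20.0% and 2/13 = 15.4%, both breaches; 2/14 = 14.3% is not. At n = 20 it takes three (3/20 = 15.0%, which is not fewer than 15%).

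**How often members would decide the 70% result in one group.** With k members in a group of n, the result turns on them when the number X of the other n − k who score 7–9 lies between r − k and r − 1, with X binomial(n − k, p). The share p is not in the document; I take 0.5 to 0.75. The contrast is all k members scoring 7–9 against none doing so.

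| n | k = 1 | k = 2 |
|---|---|---|
| 10 | 16–27% | 33–55% |
| 20 | 5–19% | 10–39% |
| 30 | 2–16% | 4–32% |

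These figures are for one group's result. A domain's status changes only if the other conditions allow it: inclusion needs every group to pass, whereas one failing group is enough to prevent it.

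**What a changed status leads to.** If round 3 settles inclusion, a member's score that completes the rule puts the domain in the set without a vote, and one that spoils it sends the domain to the meeting. If the meeting vote applies to all, both routes end in the same 70% vote. The three meeting categories carry one threshold, so sorting between them changes no stated decision rule.

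**Uptake comparison.** Clinical researcher targets sum to 20+20+10 = 50 and 30+30+20 = 80. Suppose four members (the three intervention representatives and the third Study Management Team member) all enrol as clinical researchers and all use the set. If uptake among the other participants is u, the observed rate rises by 4(1 − u)/50 to 4(1 − u)/80: 8 to 5 points at u = 0, and 4 to 2.5 points at u = 0.5. This treats enrolments as separate people who all publish trials; with fewer such people the shift is larger.

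**The case against.** The strongest defence is that the design is coherent and openly stated. The bar has one reason, a power differential, and the Background explains that Delphi anonymity can offset it. The two people with access to the data are excluded separately. Nothing in the document says that developers must stay outside the panel, and eligibility rests on expertise. All of this stands: a reader might infer a self-contradiction, and there is none.

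A reader might also infer that a few members in a small group can keep a domain out. The document does not support this. A domain that misses the inclusion rule, and is not excluded by agreement of all groups, falls under one of the meeting categories and is voted on without members. Automatic exclusion needs 70% scoring 1–3 in every group, which a few members in one group cannot produce by themselves.

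The size is also limited. Several members in one pharmacology group at its minimum size is a worst case: the three intervention representatives presumably differ in field, and the Public Research Partners, who did most to shape the list, would join user groups of 30–90. The group's role in new items is confined to uncertain cases, and the text does not show that the third Study Management Team member codes proposals. The uptake study is only an aspiration.

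What the defence leaves unanswered is that enrolled members' scores enter the round-3 rule, and that members could be counted in the participating group. A with-and-without tally may be planned in a fuller document not shown, so its absence from the article is not itself the point.

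**Conclusion.** The point holds in a limited form. The permission lets up to seven people who helped to build the instrument contribute to the round-3 result. It can alter whether a domain meets the inclusion rule, chiefly in the pharmacology professional groups, where one score is worth 5 to 10 points and two low scores breach the 15% limit for n = 10 to 13. It does not make the protocol inconsistent, and it does not let members exclude a domain by themselves. Its weight depends on which of the two statements in Consensus criteria governs: it is greater if round 3 settles inclusion, and small if every such domain still needs 70% at the meeting.

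The bias in the uptake comparison has a clear direction, towards an effect of participation, but arises only if enrolled members are clinical researchers and are counted as participants. The size of both effects rests on assumed enrolment, and the probabilities also on the assumed p. The evidence does not require that members' scores be barred outright; that is a debatable trade-off, since it removes eligible experts and users from groups that are already small.

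**What to change.** 1. Flag Steering Group records in the dataset. Recruitment methods already records journal editors so that their responses can be examined as a subgroup; the same device serves here.
2. Apply the round-3 rule with and without flagged records, in each survey in which a member enrolled, and report every domain whose status changes. State in advance which tally governs.
3. Reconcile the two statements in Consensus criteria on whether domains that meet the round-3 inclusion rule are settled or still voted on.
4. Leave Steering Group members out of the participating group in the uptake analysis.

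The cost is a dataset flag, one extra tabulation and some protocol wording. The uptake comparison loses a few researchers, at most four on the assumption above. The with-and-without tally does not undo any influence of members' scores on other panellists through the feedback histograms, and the report should say so. Recruitment was open at submission, so flagging is practicable without disturbing anyone already enrolled.
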